### 3.3. Embedding FAIR-Birth in Midwifery-Led Antenatal Care

The FAIR-Birth intervention is not designed as a standalone person-facing technology. It is an ABP instrument and an ABP document, delivered through the FAIR-Birth application, embedded within midwifery-led antenatal care. The midwife’s contribution will be central to the intervention: the midwife has to introduce the ABP process at an antenatal appointment, facilitate discussion of the developing ABP document at subsequent appointments, and support its integration into the clinical record. This model is consistent with evidence on the effectiveness of midwife-led continuity of care [9] and with the broader move toward person-centred, relationship-based perinatal care [47].

Once completed and discussed, the ABP document is stored in the electronic patient record (TI-ePA) and available to the clinical team at birth. It gives the birthing person’s prior-articulated preferences a route into a care encounter where the team is otherwise meeting them for the first time [12].

## 4. Proposed Development and Evaluation Methodology

The proposed methodology will develop and feasibility-test the FAIR-Birth intervention in two phases. Phase 1 covers systematic development of the ABP instrument, the knowledge base supporting the FAIR-Birth application, and the technical platform itself, through participatory and iterative methods. Phase 2 examines whether the integrated FAIR-Birth intervention is feasible and acceptable in routine midwifery-led antenatal care, and generates the parameters needed to plan a future randomised controlled trial. The following section describes the designed methodological framework (Section 4.1), the planned four Phase 1 workstreams (Section 4.2), and the planned Phase 2 feasibility study (Section 4.3).

### 4.1. Methodological Framework

The FAIR-Birth intervention is conceptualised as a complex intervention in the sense of the updated Medical Research Council (MRC) framework [48]. Complex interventions have multiple interacting components, variable outcomes, and are sensitive to context and to the agency of those who implement them [49]. The FAIR-Birth intervention aims to meet these criteria: it comprises a digital tool, a structured dialogue process, a clinical workflow integration within midwifery-led care, and a multilingual knowledge infrastructure that together support pregnant persons in articulating birth preferences.

The study corresponds to Phase 1 (development) and Phase 2 (feasibility and piloting) of the MRC framework. Phase 3 (full RCT evaluation) is the intended follow-on research. Ethical analysis is integrated with empirical inquiry as concurrent rather than sequential activities, following Kuehlmeyer et al. [50]. Questions about the application’s legitimate scope, the consent procedures for participants with limited German or digital literacy, and the use of preference data for system refinement will be addressed within technical and clinical workstreams (Section 4.2 workstream 4, Section 4.3).

### 4.2. Phase 1: Systematic Development (Months 1–18)

Workstream 1: Systematic literature review

A systematic review will establish the evidence base and identify design principles. The review will follow PRISMA 2020 guidelines [51] and address three questions: (a) What instruments exist for structured preference articulation in maternity care? (b) What design principles characterise effective instruments? (c) What evidence exists on their implementation feasibility? The review will include all study designs reporting on instruments or digital tools for birth-preference articulation. Methodological quality will be appraised with design-specific tools (CASP [52], MMAT [53], JBI [54]). Given the expected heterogeneity, no meta-analysis is planned; findings will be combined through structured narrative and thematic synthesis. Eligibility criteria, appraisal, and synthesis will be pre-specified in a dedicated review protocol, prospectively registered (e.g., PROSPERO), and reported per PRISMA-P.

Workstream 2: Participatory instrument development

The guiding question is: What are the design principles and content requirements for the ABP instrument from the perspectives of key stakeholders? Three focus groups (n ≈ 6–10 each) will be conducted with purposively sampled stakeholders: pregnant persons aged 18 or older (varying in migration background and health literacy), practising midwives, and obstetric clinicians, recruited through antenatal clinics and cooperating midwifery practices. The focus groups are a participatory development activity generating design requirements; sample size is justified by information power [55] rather than by data saturation [56]. Analysis will follow a structured content-analytic approach, with reflexive thematic analysis [56,57] where deeper interpretive work is warranted. Patient and Public Involvement (PPI) will be integrated throughout [38]. A schematic logic model linking the intervention’s mechanisms, intermediate outputs, and feasibility outcomes will be developed collaboratively within this workstream and finalised prior to the Phase 2 feasibility study, ensuring it reflects the priorities of the participatory development partners rather than being specified a priori.

Workstream 3: Knowledge base development and Delphi validation

A curated, multilingual knowledge base on common obstetric interventions will be developed through structured evidence synthesis, with expert validation to support clinical appropriateness across health literacy levels. A two-round online Delphi study (target n = 15–25 per round) will assess content validity and clinical appropriateness [58]. Consensus will be defined as ≥75% agreement per item. Items not reaching consensus in round one will be revised on panel feedback and re-rated in round two. The study team will recruit the panel from midwifery, obstetrics, and health-information specialisms; eligibility requires at least five years of relevant clinical or methodological experience, or a documented record in obstetric evidence synthesis or health-information development.

Workstream 4: Technical development and usability testing

The LLM-based dialogue system will be developed iteratively from RAG-based deployment, as described in Section 3.2. This workstream addresses whether the FAIR-Birth application supports structured preference articulation in a way that is usable and acceptable for pregnant persons and midwives. Usability will be assessed with the MARS Scale [59] (target n = 10–15 per round, iterative refinement between rounds). The MARS was selected over general-purpose instruments such as the System Usability Scale because it was developed specifically for mobile health applications; scores will be interpreted descriptively against its subscale structure.

### 4.3. Phase 2: Feasibility Study (Months 19–30)

A prospective, mixed-methods feasibility study will be conducted with the developed ABP instrument across two perinatal centres in Bavaria. The study will follow a sequential explanatory mixed-methods design [60]. Quantitative feasibility data will be collected first and subsequently elaborated through qualitative inquiry.

Setting and participants

Two level I/II perinatal centres in Upper Bavaria (approximately 1500–3000 births per year) have been identified as study sites. Eligible participants are pregnant persons in their second or third trimester in routine antenatal care; purposive sampling will ensure representation across migration history and health literacy. A target sample of n = 30–50 is planned. As this is a feasibility study, no power calculation is required; sample size is justified by the study’s objectives—estimating recruitment rates, assessing acceptability, and identifying procedural uncertainties for the planned trial [61].

Quantitative feasibility outcomes

Quantitative feasibility data will be collected across four domains: recruitment (proportion of eligible and approached pregnant persons who consent; retention over the antenatal period), engagement with the FAIR-Birth application (completion of the ABP process; time spent in each ABP stage), procedural feasibility (data completeness; technical errors; midwife workload), and acceptability (Mobile App Rating Scale [MARS] [59] scores from pregnant persons and midwives). The four feasibility domains above (recruitment, engagement, procedural feasibility, and acceptability) constitute the primary feasibility signals informing the progression decision. The pilot psychometric measures introduced below are explicitly subordinate to a parameter-estimation role: they are collected to estimate variance and the plausible range of effect sizes for the future randomised controlled trial sample-size calculation, and are expressly not used to test effectiveness.

Equity-related process indicators will be collected alongside these outcomes: the proportion accessing application content in languages other than German, uptake of supported-access pathways (midwife-assisted onboarding, paper-based fallback), and the proportion recruited via midwifery practices serving underserved populations. Where cell sizes allow, completion and acceptability will be reported descriptively by language group, education, and migration history, without inferential comparison.

Pilot data on the Birth Satisfaction Scale-Revised (BSS-R) [62] and the Wijma Delivery Expectancy Questionnaire (W-DEQ_A) [63] will also be collected. These outcomes will not be used to test effectiveness in the feasibility phase. They will be used to estimate variance and the plausible range of effect sizes, informing the sample-size calculation for the planned randomised controlled trial.

Progression decision

This study will not pre-specify numeric pass/fail thresholds. No prior empirical base exists for AI-supported antenatal preference articulation in multilingual midwifery-led care, so borrowed thresholds would be arbitrary; pre-specified thresholds also tend to penalise studies that sample underserved populations equitably [64]. The CONSORT extension for pilot and feasibility trials [65] frames such studies as informing future thresholds rather than passing or failing fixed ones.

The study will pre-specify a structured progression-decision process following Avery et al. [66]. At the end of Phase 2, the study team will review feasibility data, equity indicators, and qualitative interview findings against three possible verdicts: continue (recruitment achievable, application usable without structural redesign, ABP documentation adequate, midwife acceptability sufficient); amend (specific components require redesign before the RCT, but the intervention as a whole is feasible); or stop (a fundamental barrier cannot be resolved by amendment). The progression decision and the evidence supporting it will be documented in a progression report and published alongside the feasibility results, regardless of the verdict reached.

Qualitative component

Semi-structured interviews with a purposive subsample of participants (target n = 12–15) and participating midwives (target n = 6–8) will explore experiences of the ABP process, perceived utility of the FAIR-Birth application in the midwifery encounter, and barriers and facilitators to implementation. The qualitative component is exploratory and illustrative; sample sizes are justified by information power [67] rather than by an expectation of thematic saturation. Data will be analysed using reflexive thematic analysis [57].

Integration

Quantitative and qualitative data will be integrated at the interpretation stage using a joint display approach [68,69]. Qualitative findings will help to explain and contextualise the quantitative feasibility outcomes and generate recommendations for intervention refinement before the planned randomised controlled trial.

Ethics and governance

Ethics approval will be sought from the relevant institutional ethics committee prior to any data collection, in accordance with the Declaration of Helsinki and current DFG guidelines [70]. Informed written consent will be obtained from all participants. For participants with limited digital literacy, consent will be obtained through a midwife-assisted procedure in which the study information is explained verbally and questions are addressed before written consent is given. Where a participant’s preferred language is one for which application content is available but consent materials have not yet been formally validated, consent will be supported by a professional interpreter or a qualified bilingual midwife, and participation in that language will begin only once the participant has confirmed understanding; the languages affected will be documented as part of the feasibility findings. All data will be pseudonymised and stored in compliance with GDPR. The study will be prospectively registered in DRKS or ClinicalTrials.gov before recruitment commences.

Within the feasibility study, the LLM is adapted exclusively through non-training methods (Section 3.2), so participant interaction data are not used to train or fine-tune the model. The governance principles guiding this stage are transparency, explainability, and data protection. Data are pseudonymised and processed on TH Rosenheim or trusted research-cluster infrastructure, with no transfer to commercial AI providers outside the EU, and participants are informed of data handling within informed consent. Reinforcement learning from human feedback and parameter-efficient fine-tuning, if pursued at the subsequent randomised controlled trial stage, would be accompanied by a dedicated, explicit consent process for the use of interaction data in model adaptation, designed with adequate lead time.

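### The only quantitative acceptability measure in Phase 2 is an app rating scale that the plan elsewhere calls its usability measure, although the intervention to be judged is a midwife-embedded process

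*Protocol article*

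**What the plan says.** Section 4 sets Phase 2 the task of examining whether the integrated intervention is feasible and acceptable in routine midwifery-led antenatal care. Section 3.3 makes clear that this is wider than the software: "The FAIR-Birth intervention is not designed as a standalone person-facing technology". It gives the midwife three tasks: introducing the ABP process, facilitating discussion of the developing document, and supporting its integration into the clinical record.

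Workstream 4 (Section 4.2) asks whether the application is "usable and acceptable for pregnant persons and midwives", so it names two properties. It then assigns an instrument to one of them: "Usability will be assessed with the MARS Scale [59]". MARS was preferred to general-purpose tools such as the System Usability Scale "because it was developed specifically for mobile health applications", and "scores will be interpreted descriptively against its subscale structure".

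Section 4.3 lists four quantitative domains. The fourth is "acceptability (Mobile App Rating Scale [MARS] [59] scores from pregnant persons and midwives". All four are declared primary signals for the progression decision. The conditions for the *continue* verdict include "application usable without structural redesign, ABP documentation adequate, midwife acceptability sufficient". The study team will "review feasibility data, equity indicators, and qualitative interview findings against three possible verdicts".

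The qualitative component covers 12–15 participants and 6–8 midwives. Its topics are the ABP process, the application's utility in the midwifery encounter, and barriers and facilitators. The plan describes this component as exploratory and illustrative.

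**The concern.** The object to be judged and the instrument chosen to judge it do not match. The object is a facilitated dialogue, a document and a clinical workflow, delivered with the help of an app. The instrument was selected because it is specific to apps, and one phase earlier it carries the label of usability. Nothing in Section 4.3 explains the change of label, and no subscale is assigned to acceptability.

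What is at stake is the reading of a primary progression signal. If the app scores well, the acceptability domain can look favourable while saying little about whether midwives accept the added counselling and documentation work, or whether pregnant persons welcome the structured conversation. If the app scores poorly, the domain can look unfavourable although the underlying process is welcome. The *amend* verdict depends on knowing which component needs redesign, and an app score alone does not separate an interface problem from reluctance about the process.

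**Working it through.** The plan states no figure that could be reproduced on this point, so the check is a tracing of measures to constructs, with one small calculation on coverage.

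1. **Object.** Sections 3.3 and 4: the integrated intervention, with the midwife's contribution central to it.

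2. **Uses of MARS.** Section 4.2, Workstream 4: usability of the application. Section 4.3: acceptability. Both cite the same reference. Workstream 4 treats usable and acceptable as distinct, so the plan's own vocabulary does not allow one label to stand for the other without explanation.

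3. **Other quantitative data in Section 4.3 that bear on acceptance of the process.**
   - Retention (recruitment domain), and ABP completion and time per stage (engagement domain): these record behaviour and are compatible with several explanations.
   - Midwife workload (procedural domain): this records burden. A midwife may accept a heavy task or reject a light one.
   - Uptake of midwife-assisted onboarding and of the paper fallback (equity indicators): these record the access route.

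   None is a rating of acceptability by the people concerned.

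4. **Coverage of the direct evidence.** Planned enrolment is 30–50 and planned participant interviews are 12–15.
   - Smallest share interviewed: 12 / 50 = 24%.
   - Largest share interviewed: 15 / 30 = 50%.
   - Participants with no direct report on acceptability of the process: from 30 − 15 = 15 to 50 − 12 = 38.

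   For midwives the target is 6–8 interviews. The number taking part is not stated, so no share can be given.

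5. **Fit for paper users.** Section 4.3 provides a paper-based fallback, and Section 5 presents it as a mitigation for limited smartphone access and digital literacy. A person who used only paper has no app experience to rate. The article does not say how acceptability is recorded for such a person, yet acceptability is to be described by language group, education and migration history where cell sizes allow. The measure thus fits least well for people whom the equity aim has in view.

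6. **Link to the verdict.** Section 4.3 lists usability of the application and midwife acceptability as separate conditions for *continue* and ties neither to a named source.

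**The case against.** The strongest reply is that the progression decision does not hang on MARS. Section 4.3 rejects numeric thresholds and has the team weigh feasibility data, equity indicators and interviews together. The interviews ask about the ABP process and implementation barriers, which is the object at issue. The design is sequential explanatory with a joint display, so elaborating a thin score by interview is the declared method. A poor interface around a welcome process is a case the *amend* verdict can accommodate.

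Much of this stands. A reader might infer that the midwife-acceptability condition merely repeats the application-usability condition, or that one app score drives both. The article does not support that. It never assigns the Phase 2 MARS score to the usability condition; completion, time per stage and technical errors bear on that condition, and interviews and workload bear on the midwife condition. Nor can it be said that an unwelcome process would pass as acceptable, since no mechanical rule exists.

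It is also fair to say that the logic model due before Phase 2, or a fuller protocol, could map sources to conditions. That would answer the mapping question. It would not supply a process-level measure, because the article expressly fixes the acceptability domain as MARS scores. A further caution is that if few midwives take part, a mean score adds little to interviewing them. That limits the gain on the midwife side but not for the 15 to 38 participants who will not be interviewed.

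**Conclusion.** The point holds as a mismatch between construct and measure. One of the four primary feasibility domains is quantified only by a scale that the plan justifies as app-specific and elsewhere labels usability, while the question asked concerns a midwife-embedded process. Direct evidence on acceptance of that process comes from 24% to 50% of participants and from 6–8 midwives, in a component the plan calls exploratory; the remaining evidence is indirect.

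It does not show that two conditions for continuing duplicate each other, or that any verdict would be wrong. The conclusion rests on the plan's own description of MARS. The items are not in the article, and nothing is claimed about their content. It also assumes that some participants may use paper without the app, which the article allows for but does not quantify. This is worth correcting before Phase 2, but it does not undermine the feasibility study as a whole.

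**What to change.** Three changes to Section 4.3:

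- Label MARS in Phase 2 as a measure of app usability or quality, consistent with Workstream 4.
- Add a short intervention-level acceptability measure, worded for the ABP conversation, document and workflow. Give it to all enrolled persons, including paper users and those who stop, and to all participating midwives. Report it descriptively, with no threshold, in keeping with the progression approach.
- State that sufficient midwife acceptability is judged on that measure together with the midwife interviews and the workload data.

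The cost is a few extra items per respondent and their translation into the study languages, with the usual care over comparability between languages. Section 1 says that funding and ethics approval are still to come and that methodological scrutiny is invited, so the change can be made before any data are collected.

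### Phase 2 as described has no comparator, so BSS-R and W-DEQ_A can supply an SD but not a range of effect sizes for sizing the RCT

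*Protocol article*

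**What the plan says.** All the relevant text is in the protocol article.

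- **Design (Section 4.3, opening).** "A prospective, mixed-methods feasibility study will be conducted with the developed ABP instrument across two perinatal centres in Bavaria". No control group, allocation or historical comparison is described. Section 4.1 places the controlled evaluation later: "Phase 3 (full RCT evaluation) is the intended follow-on research".
- **Sample (Section 4.3, Setting and participants).** "A target sample of n = 30–50 is planned", and "purposive sampling will ensure representation across migration history and health literacy". The size is justified by three aims: "estimating recruitment rates, assessing acceptability, and identifying procedural uncertainties for the planned trial". Neither variance nor effect estimation is among them.
- **Pilot scales (Section 4.3, before Progression decision).** "Pilot data on the Birth Satisfaction Scale-Revised (BSS-R) [62] and the Wijma Delivery Expectancy Questionnaire (W-DEQ_A) [63] will also be collected". Measurement times are not given.
- **Use of the scales.** This is stated twice in Section 4.3. The first paragraph under Quantitative feasibility outcomes says "they are collected to estimate variance and the plausible range of effect sizes for the future randomised controlled trial sample-size calculation". The paragraph that introduces the two scales says "They will be used to estimate variance and the plausible range of effect sizes, informing the sample-size calculation for the planned randomised controlled trial". Both places add that the scales will not serve as a test of effectiveness.

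**The concern.** A two-arm trial is sized on two quantities: the difference between arms that it must be able to detect, and the SD of the outcome. The protocol says the pilot data will inform both. A cohort in which everyone is offered the intervention carries information on the second but none on the first, because nothing in it shows what scores would have been without the intervention.

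At stake is the input to the next trial. If a before-after shift, or a cohort mean set against an outside value, were carried forward as the effect, the RCT could be sized on a quantity that is not a treatment effect. Required size is very sensitive to that input, as the working shows. This is a stated use that the described design cannot support, so it is not a detail that a fuller protocol or analysis plan would fill in.

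**Working it through.** The plan gives no computed figure for this point, and its n = 30–50 has no power basis, so there is nothing to reproduce. The inputs from Section 4.3 are n = 30 to 50, one group, and two scales with unstated timing. The illustrations assume SD = 1, two-sided alpha 0.05, 80% power, 1:1 allocation and roughly normal scores. None of these is in the document.

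**1. What one group identifies.** The RCT needs δ = (mean with intervention) − (mean without). Phase 2 observes only the first term, so δ is not identified, whatever the n.

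- *BSS-R.* By its name it rates satisfaction with the birth, so there is no earlier value to subtract. All that is available is a mean, with 95% half-width t(0.975, n−1)/√n = 0.37 SD at n = 30 and 0.28 SD at n = 50. A mean is not a contrast.
- *W-DEQ_A.* If it were measured twice, the mean change would have half-width t(0.975, n−1)·√(2(1−ρ))/√n. At an assumed ρ = 0.5 this is 0.37 SD (n = 30) or 0.28 SD (n = 50). At ρ = 0.7 it is 0.29 or 0.22 SD. The change may be estimated fairly precisely, but it sums any intervention effect with the course of pregnancy and routine antenatal care, and these cannot be separated.

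**2. Would a comparator of this size have helped?** This is hypothetical, since nobody proposes it. Splitting the sample 1:1 gives a half-width near d = 0 of 1.96·√(2/m):

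- m = 15 per arm: 1.96 × √(2/15) = 0.72 SD
- m = 25 per arm: 1.96 × √(2/25) = 0.55 SD

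**3. Sensitivity of RCT size to the effect.** Per-arm n = 2(1.96 + 0.842)²/d² ≈ 15.7/d², rounded up:

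| d | per arm |
|---|---|
| 0.2 | 393 |
| 0.3 | 175 |
| 0.4 | 99 |
| 0.5 | 63 |
| 0.8 | 25 |

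Moving d from 0.2 to 0.5 changes the size by 393/63 ≈ 6.2-fold. Even the hypothetical split would leave d uncertain by more than that span.

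**4. What the pilot can deliver.** The 95% CI for σ is s·√((n−1)/χ²(0.975)) to s·√((n−1)/χ²(0.025)):

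| n | SD multiplier | N multiplier (its square) |
|---|---|---|
| 30 | 0.80 to 1.34 | 0.63 to 1.81 |
| 50 | 0.84 to 1.25 | 0.70 to 1.55 |

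So the variance role can be met, with limited precision. The intervals assume that every participant supplies the scales. Section 4.3 treats retention and data completeness as unknowns, so the real intervals may be wider. Purposive sampling may also make the SD differ from that of an RCT population.

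**The case against.** **The scales are declared subordinate and are not used to test effectiveness.** True, but the objection is to estimating an effect for planning. Renouncing a test does not create a contrast.

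**The data only inform the calculation.** The wording does not exclude external evidence or a minimally important difference, and this part stands: the document does not say the RCT will be sized on a pilot effect alone. A charitable reader might also take the phrase to mean that the pilot SD will be used to standardise differences taken from elsewhere. But both sentences make the pilot data the source of the effect-size range and name no other source. If the charitable sense is meant, the text should say so.

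**Single-arm is an inference.** It is. The term is not used, measurement times are not given, and the document describes BSS-R only by name. Still, no second group appears anywhere, and the controlled comparison is assigned to follow-on work.

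**Stronger readings that a reader might infer.** Three are tempting, and the documents support none of them.

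- *The RCT will probably be underpowered.* This is not shown. With a correctly chosen target difference and the point-estimate SD, mean true power is still about 78–79%. No power loss can be computed for the effect-size problem itself, because no pilot effect exists yet.
- *The silence on SD imprecision is a defect.* Handling that imprecision properly belongs to the RCT's own plan, and an upper confidence limit is only one of several conventions.
- *The feasibility study is compromised.* It is not. The four feasibility domains are the primary signals, and the continue, amend and stop criteria use neither scale.

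**Conclusion.** The point holds in a narrow form. In two places Section 4.3 assigns the pilot scales a task that the described design cannot perform: a between-group effect, or a range for one, is not identifiable from one treated cohort at any n. The other task, estimating variance, is legitimate, with 95% limits of about 0.80–1.34 times the estimate at n = 30 and 0.84–1.25 times at n = 50.

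The conclusion rests on Phase 2 having no comparator, which is how the article reads, and on BSS-R being a rating of the birth. The interval figures further assume roughly normal scores and complete data. It should be fixed before the study starts, but it is not critical: no participant, primary feasibility outcome or progression verdict is affected, and any harm would arise only when the RCT is sized.

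**What to change.** In both sentences of Section 4.3, remove the reference to effect sizes so that the stated role ends at variance. Then add:

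1. The target difference for the RCT will be an important difference justified independently of these data, from external evidence and with the PPI partners.
2. BSS-R and W-DEQ_A will each contribute an SD reported with its 95% confidence interval and the number of participants on which it rests.

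How the RCT allows for imprecision in that SD, for example by using an upper confidence limit, can be settled when the RCT is planned. If the authors meant only that the pilot SD would standardise differences taken from other sources, one clause saying so would also resolve the point.

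The cost is a change of wording in two sentences and a short addition. The sample, data collection, feasibility outcomes and progression process of Phase 2 stay as they are.
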